### Outcomes {12}

The primary outcome is per-capita annual household expenditure, which is arrived at by dividing the total annual household expenditure by the number of individuals that habitually reside in the household. Expenditures covered include food items, non-food household items (e.g. electricity, utilities), healthcare, and education, collected in Ugandan Shillings. Amounts are adjusted for inflation and expressed as constant 2017 purchasing power parity (PPP) United States Dollars. Household expenditure has a closer link with household well-being and is often used to evaluate transfer programmes. Household poverty status will also be derived, whether per-capita consumption expenditure is below US$1.90 per day and the household poverty gap, the shortfall in per-capita consumption expenditure from the poverty line—US$1.90 per day. Further secondary outcomes measure anticipated changes based on the theory of change. These are annual household income from agricultural and non-agricultural sources in the last 1 year preceding the survey (household level); participation in livelihood activities by project participants; participation in social activities by project participants in the last 1 week preceding the survey; and the health and well-being of project participants. For the process evaluation, outcomes include the programme’s fidelity, reach, and dose; mechanisms of impact (e.g. mediators); and context-dependencies (e.g. moderators).

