The results from the simulated analyses are shown in Fig. 3. The darker CIs correspond to scenarios with higher ICCs. Estimates were precise when the pre-post correlation was high (right-hand panel), and sufficiently precise to exclude the null with a low correlation and true effect of a difference between the arms of 0.1 standard deviation of per-capita expenditure at baseline (left-hand panel). Under conservative assumptions, we would reject the null hypothesis at conventional levels (*p* < 0.05) if the true effect of the intervention on per-capita expenditure was at least 0.1 standard deviations of the baseline distribution. This effect size is similar in magnitude to the overall effect on per-capita expenditure found in trials of the original (non-inclusive) version of the programme [1]; therefore, this trial would have sufficient power to detect an effect if the adaptations of the intervention for people with disabilities worked such that the effect was as strong as it had been for people without disabilities.

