## Statistical methods

### Statistical methods for primary and secondary outcomes {20a}

For basic description, we will report the mean and standard deviation (or median and interquartile range) for continuous variable and the number and percentage for categorical variables, by intervention status (yes or no), and by data wave (baseline vs follow-up). We will test the balance of the covariates by *t*-test (or Mann Whitney *U* test) for continuous variables and by chi-square test for any categorical variables. Covariates include socio-demographic factors (e.g., age, sex), as well as any other factors likely to affect the implementation of the intervention.

Data will be fitted with multi-level linear regression to test the effect of the intervention, with the difference of the primary or secondary outcomes between follow-up and baseline as the outcome, and intervention status as the exposure, controlling for potential imbalance in covariates at baseline. To account for the data structure, we will consider the random intercept and random slope for exposure at the level of district and pair indicators. To address multiplicity concerns the Bonferroni Correction or Bayesian modelling approaches will be applied. The model’s adequacy will be assessed through residual plots, with log transformations of variables considered if residuals are not randomly distributed. All analysis will be conducted in Stata and R. We will report the estimation as coefficient for continuous outcome and OR for binary outcome, as well as their 95% confidence interval (CI). *P* value < 0.05 will the level of statistical significance.

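### The multiplicity rule is an open choice between Bonferroni and Bayesian modelling, not tied to the stated 0.05 level and 95% intervals, so the criterion for the primary outcome is not fixed

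*Protocol article*

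**What the plan says.** Statistical methods for primary and secondary outcomes {20a} describes one multi-level linear model for all outcomes, "with the difference of the primary or secondary outcomes between follow-up and baseline as the outcome". It continues: "To address multiplicity concerns the Bonferroni Correction or Bayesian modelling approaches will be applied". The same paragraph asks for 95% confidence intervals on every estimate and closes with the threshold: P "value < 0.05 will the level of statistical significance". Nothing connects the multiplicity sentence to the threshold or to the intervals.

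Other sections bear on which tests might be corrected:

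- Outcomes {12} names one primary outcome: "The primary outcome is per-capita annual household expenditure". It adds two derived poverty measures ("Household poverty status will also be derived", and a poverty gap) and four further secondary headings: income, livelihood participation, social participation, and health and well-being.
- Objectives {7} places three constructs under the primary objective: expenditure, livelihood and social participation.
- Trial design {8} sets two endline surveys. The first covers participants with disabilities only and the second covers everyone.
- Sample size {14} bases its precision statement on per-capita expenditure alone. If the true effect is at least 0.1 baseline standard deviations, "we would reject the null hypothesis at conventional levels", given there as p < 0.05.

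**The concern.** The two approaches on offer are not interchangeable. Bonferroni compares each p-value with 0.05/m, and its matching intervals are wider than 95%. A Bayesian model does not in itself produce a p-value to compare with 0.05. A commitment to one or the other, with no rule for choosing, does not settle what counts as a positive result.

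The headline conclusion on expenditure is at stake. The multiplicity sentence stands under a heading that covers primary and secondary outcomes and does not exempt the primary outcome. A reader therefore cannot tell whether a primary p-value of, say, 0.02 is a success. The timing adds weight. Who will be masked {17a} says there is no masking of households and participants after allocation, and Trial status says the first endline was carried out in July 2022. Unless a dated analysis plan settles the choice, it could be made with outcome data in hand.

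**Working it through.** **Inputs from the protocol.** Significance level 0.05 and 95% intervals ({20a}); one primary outcome, two derived poverty measures and four further secondary headings ({12}); three constructs in the primary objective ({7}); two endlines ({8}). Sidedness is not stated. I assume two-sided tests, as the intervals suggest.

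**Step 1: the stated figures agree with each other.** 1 − 0.95 = 0.05, so the threshold and the interval level match for a single unadjusted test.

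**Step 2: size of the possible family (assumption).** The protocol gives no m. Candidates are:

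- m = 1: the primary outcome stands alone.
- m = 3: the constructs in the primary objective.
- m = 7: the listed outcomes, 1 + 2 + 4. This grows if income or health and well-being is split.
- m = 14: 7 outcomes × 2 endlines. The two endlines cover different populations, so this family is the most speculative.

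**Step 3: thresholds and matching intervals.** Threshold = 0.05/m; interval level = 1 − 0.05/m.

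| m | Threshold | Matching interval | Zone where the primary verdict is open |
|---|---|---|---|
| 1 | 0.05 | 95% | none |
| 3 | 0.0167 | 98.33% | 0.0167 to 0.05 |
| 7 | 0.0071 | 99.29% | 0.0071 to 0.05 |
| 14 | 0.0036 | 99.64% | 0.0036 to 0.05 |

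The last column applies only if the primary outcome is inside the Bonferroni family and 0.05 is read as a nominal per-test level.

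**Step 4: cost to the primary test, for illustration only.** The protocol states no power figure. Take a test with 80% power at two-sided 0.05, so that its expected z is 1.960 + 0.842 = 2.802. Power at a stricter threshold is Φ(2.802 − z), and the minimum detectable effect changes by the ratio (z + 0.842)/2.802.

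- m = 3: z = 2.394; power Φ(0.408) = 66%; ratio 3.236/2.802 = 1.15.
- m = 7: z = 2.690; power Φ(0.112) = 54%; ratio 3.532/2.802 = 1.26.
- m = 14: z = 2.914; power Φ(−0.112) = 46%; ratio 3.756/2.802 = 1.34.

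**Step 5: comparison with the sample size section.** The precision statement uses p < 0.05 on expenditure. It matches m = 1, or a nominal 0.05. It would not match a Bonferroni threshold applied to the primary outcome.

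**The case against.** The strongest reply is that nothing conflicts. A level of 0.05 sits comfortably beside Bonferroni if it is the family-wise rate or the cut-off for adjusted p-values, and both are ordinary usage. It also fits if expenditure is tested alone, which is how Sample size {14} treats it. The multiplicity sentence names no family, so the presence of the primary outcome in it is inferred from the section heading and the model sentence. The document is a condensed article, and an analysis plan that is not shown may list the family and the interval convention.

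Most of this stands. A reader might infer that the section contradicts itself, so that one p-value is both significant and not significant. The text does not support that, because each reading above reconciles it. A reader might also infer that the secondary claims go uncontrolled, but the protocol does commit to some form of control. Nor is a lower limit near 0.004 a figure from the protocol: it needs about 11 to 14 tests.

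The reply does not remove the open choice itself. The article commits in print to one of two approaches that work differently, beside an unlinked threshold, and the text favours none of the reconciling readings. That goes beyond detail left to an analysis plan.

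One further objection is fair. Naming expenditure as the sole primary outcome is not enough while it is measured at two endlines. Two unadjusted 5% tests would carry up to 1 − 0.95² = 9.75% if independent. The fix therefore has to name the endline and the population.

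**Conclusion.** The concern holds as an unreconciled decision rule. The protocol does not fix which multiplicity approach applies, whether the primary outcome is in the corrected family, or what the 0.05 and the 95% intervals refer to. If the primary outcome is in a Bonferroni family and 0.05 is nominal, a primary p-value between 0.05/m and 0.05 can be called either way. The lower limit is 0.0167, 0.0071 or 0.0036 for assumed families of 3, 7 or 14 tests. The zone vanishes if the primary outcome stands alone. The power losses in the working rest on a hypothetical 80% starting point and are not results for this trial. Bonferroni over the primary outcome would also not match the level behind the precision statement. The point should be settled, since the main conclusion may turn on it and settling it costs very little.

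**What to change.** Replace the multiplicity sentence with one rule:

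- **Primary test.** Per-capita expenditure at one named endline and in one named population, two-sided 5%, with a 95% confidence interval and no adjustment. Sample size {14} is built on households where the project participant is a person with disabilities, so the named population should be reconciled with that. Expenditure at the other endline is secondary.
- **Secondary outcomes.** The listed outcomes form one family, tested with Holm at two-sided 5% in place of Bonferroni and reported with adjusted p-values. Unadjusted 95% intervals are labelled descriptive. Holm gives the same family-wise control and is never less powerful. In an illustrative simulation of six outcomes (correlation 0.5, each with 80% power unadjusted), average power was 67% with Holm against 56% with Bonferroni.
- **Bayesian modelling.** Keep it only as a labelled sensitivity analysis, not as an alternative rule for error control.
- **Cross-reference.** State that the precision statement in Sample size {14} refers to this unadjusted primary test.

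The cost is a few sentences and no new data. The downside is that some secondary outcomes with nominal p just under 0.05 will not be called significant.

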Available data from the screening and verification visits informed the estimated total number of clusters that would be needed to reach 5400 eligible households. During the screening and verification process, BRAC Uganda found that approximately 25% of project participants were people with disabilities, and as such it was expected that the trial would include 675 people with disabilities in each arm. The distribution of eligible households per village was used to simulate the trial, 185 villages sampled with replacement from the verified villages gave approximately 5400 research participants in a simulated trial. A value of 0.8 was used from a recent evaluation of the graduation programme in Ghana for the standard deviation of the distribution of the normalised per-capita expenditure at baseline [10]. Since the degree of clustering in the outcome was unknown, the intraclass correlation coefficient (ICC) was allowed to vary between 0.05 and 0.3. The estimated between-village variation in mean level of the outcome at baseline and individual-level outcomes were drawn from the village-level means with a constant within-village variance. The endline results were generated using the simulated baseline data and a covariance matrix with a pre-post correlation of either 0.4, 0.6, or 0.8. The 185 clusters were pair-matched by the number of people with disabilities and a constant intervention effect was applied to the clusters allocated to the intervention arm. The intervention effects ranged from a difference between the intervention and control arms in the mean per-capita expenditure of zero standard deviations of the baseline per-capita expenditure, to 0.2 standard deviations, which is as high as the largest effects on per-capita expenditure observed in previous trials [1]. Multi-level linear regression was used to estimate the effects, controlling for baseline per-capita expenditure, accounting for clustering with a village-level random effect, and for the randomised design with fixed-effect for the pairs.

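### If the frequentist multiplicity option is used, Holm's step-down procedure should replace single-step Bonferroni for the secondary outcomes

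*Protocol article*

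**What the plan says.** The multiplicity plan is one sentence in *Statistical methods for primary and secondary outcomes {20a}*: "To address multiplicity concerns the Bonferroni Correction or Bayesian modelling approaches will be applied". These are two alternatives with no choice made. The family is not defined, and the text does not say whether the primary outcome belongs to it. The same paragraph gives the significance level ("value < 0.05 will the level of statistical significance") and says estimates will be reported "as well as their 95% confidence interval (CI"), with no adjusted level for either.

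*Outcomes {12}* names one primary outcome: "The primary outcome is per-capita annual household expenditure". Two further results are computed from the same quantity: "Household poverty status will also be derived, whether per-capita consumption expenditure is below US$1.90 per day and the household poverty gap". Then comes "Further secondary outcomes measure anticipated changes based on the theory of change", followed by four items: household income, participation in livelihood activities, participation in social activities, and health and well-being. Counting each item once gives six results besides the primary.

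**The concern.** Bonferroni compares every p-value with 0.05/k, where k is the number of tests in the family. Holm gives the same family-wise guarantee with thresholds that relax after each rejection. If Bonferroni is the option chosen, it is never better as a testing rule, and it can miss effects that Holm would declare.

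The outcomes affected matter here. *Objectives {7}* places livelihood and social participation in the primary objective, but *Outcomes {12}* lists them as secondary, where a correction would bear on them. *Sample size {14}* says the size of the study is fixed by programme funding, so power given up in the analysis cannot be recovered by enrolling more households. The calculations there cover only per-capita expenditure at an unadjusted 5% level, so nothing shows spare power for the secondary outcomes.

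A separate and conditional issue concerns the two poverty measures. If they are counted in the family, they tighten the threshold for the other four although they re-express expenditure data already tested as the primary outcome.

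**Working it through.** **The plan's own figures.** *Sample size {14}* says "it was expected that the trial would include 675 people with disabilities in each arm"; 0.25 × 2700 = 675 reproduces this. No power is stated for any secondary outcome, so there is no planned figure to reproduce on this point.

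**Step 1: why Holm dominates, for any family.** Order the p-values from smallest to largest and compare the i-th with 0.05/(k − i + 1), stopping at the first failure. For k = 6 the thresholds are 0.0083, 0.0100, 0.0125, 0.0167, 0.0250 and 0.0500.
- Every threshold is at least 0.05/6, so any p-value that passes Bonferroni also passes Holm.
- Suppose m of the null hypotheses are true. When the first true one is rejected, at least m hypotheses remain, so its p-value is at most 0.05/m. The probability that any of m true nulls gives such a p-value is at most m × 0.05/m = 0.05, with no assumption about dependence.
- The first threshold is the same for both methods, so the chance of at least one rejection is identical.

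**Step 2: Bonferroni power.** Assume 80% unadjusted power at two-sided 5% (the protocol does not state sidedness). The mean of the test statistic is 1.960 + 0.842 = 2.802. Power at level 0.05/k is Φ(2.802 − z), where z is the two-sided critical value.

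| k | Level | z | Power |
|---|---|---|---|
| 6 | 0.0083 | 2.638 | Φ(0.164) = 56.5% |
| 4 | 0.0125 | 2.498 | Φ(0.304) = 61.9% |

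**Step 3: Bonferroni against Holm, k = 6.** Holm has no such closed form, so correlated normal test statistics were simulated. The assumed correlations were 0.7 to 0.9 between the two poverty measures and 0 to 0.3 otherwise. Power is the average over the real effects, or equivalently power for one non-derived outcome when all are affected alike.

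| Real effects, each at 80% unadjusted power | Bonferroni | Holm |
|---|---|---|
| All six | 56% | 67-68% |
| Four, poverty measures null | 56% | 61-62% |
| Three of six | 57% | 60% |

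The 56% and 57% for Bonferroni are the same quantity, 56.5%, apart from simulation error. With 50% unadjusted power and all six effects real, Holm gains 3 to 5 points. With no real effects, the family-wise error at k = 6 is the same for both methods, 0.043 to 0.049 depending on the correlations.

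**Step 4: the two derived measures.** Taking them out moves the first-step threshold from 0.05/6 = 0.0083 to 0.05/4 = 0.0125. Power for a remaining outcome, all real at 80% unadjusted, is then 62% with Bonferroni and 72-73% with Holm.

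**The case against.** The strongest reply is that nothing here is invalid. Bonferroni controls the family-wise error, it is only one of two open options, and an article may leave the exact procedure and the family to an analysis plan. The first two parts stand. A reader might infer that the protocol commits to Bonferroni and so is already losing power. The text does not support that: the loss arises only if Bonferroni is chosen over Bayesian modelling. The point survives because Bonferroni is the only frequentist method named and the comparison with Holm does not depend on the family.

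A reader might also infer that the poverty measures are already using up the error rate. With no family defined, that cannot be read from the document. Nor does Holm cure it, since plain Holm makes no use of correlation. Only removing those outcomes, or in part a resampling method, addresses it. Removal has a price too: poverty status and poverty gap describe the lower part of the distribution, can move differently from the mean, and would lose the protection of the correction.

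It would be too strong to say that Bonferroni gives up power for nothing. It has simple matching simultaneous intervals, and Holm does not. That advantage is real, although the protocol states 95% intervals with no adjusted level and so shows no plan to use it.

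Finally, the largest gain needs all six effects to be real. *Background and rationale {6a}* reports that earlier trials did not improve physical health, and health is among the six.

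**Conclusion.** The point holds conditionally. If the frequentist option is used, Holm is the better rule for any family of two or more tests, at the same family-wise error. That part needs no assumption about effects or correlations.

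The size of the gain does need assumptions: six secondary outcomes in the family, 80% unadjusted power for each real effect, and the stated correlations. On that basis average power rises by about 11 to 12 points if all six effects are real, about 5 if the two poverty measures are null, and about 3 if only three effects are real. The chance of finding at least one effect does not change. The gain from setting the two poverty measures aside is a separate matter and arises only if they would otherwise be in the family. This is an improvement to a valid method, worth making because it costs little. It is not an error that threatens the primary result.

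**What to change.** In *Statistical methods for primary and secondary outcomes {20a}*, replace the Bonferroni correction with Holm's step-down procedure for the secondary outcomes, or with a step-down resampling method that uses their correlation. Leave the Bayesian option untouched.

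If poverty status and poverty gap would otherwise be in the corrected family, state that they are reported outside it as supportive re-expressions of the primary outcome, with no separate confirmatory claim.

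The change takes a sentence or two and no extra data. It has two costs:
- **Intervals.** The 95% intervals shown would be unadjusted and may not agree with the Holm decisions. The report should say so.
- **Timing.** *Trial status* records that the first endline survey took place in July 2022, and *Who will be masked {17a}* says allocation is not masked. A move to a more permissive rule should therefore be dated and fixed before the endline data are analysed.

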### Interim analyses {21b}

No interim analyses.

### Methods for additional analyses (e.g. subgroup analyses) {20b}

Subgroup analyses will be conducted to ascertain the differential efficacy of the intervention. These analyses will include stratification by sex, disability status (whether the household has people with disabilities), and by whether the recipient of the intervention is the person with disabilities within the household. The objective of these subgroup analyses is to elucidate whether the intervention’s effectiveness varies across these distinct demographic segments, thereby providing a deeper insight into its targeted impact.

For the process evaluation, we will combine data sources to determine fidelity, reach and dose, in order to describe the actual intervention as experienced by programme participants. To identify mechanisms of impact, we are working with the FCDO-funded POInT (process-outcome integration with theory) project led by LSHTM [13], to build a framework for jointly interpreting certain aspects of the qualitative and quantitative data gathered to make inferences about the causal pathways that are most important for this intervention to work (mediators). Similarly, for general theoretical learning, we will use qualitative data to learn about unexpected context contingencies, and quantitative data to explore moderation by contextual factors.

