### Objectives {7}

The aim of the impact evaluation is to estimate the effect of the DIG Programme on the livelihoods and well-being of people with disabilities and their families in Uganda. Consequently, the primary objective is to estimate the effect of the DIG programme on per-capita expenditure, livelihood, and social participation of people with disabilities and their families. The secondary objective of the impact evaluation is to estimate the differential effect of the DIG programme on per-capita expenditure, livelihood, and social participation of people with disabilities and their families, compared to the effect among people without disabilities. The study is complemented by a process evaluation. The objectives of the process evaluation, in accordance with MRC guidance for process evaluations of complex interventions [8], are to describe the intervention implementation as delivered, test evaluation hypotheses, and generate theoretical learning to inform future intervention designs.

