### Trial design {8}

The overall effect of the intervention is estimated using a two-arm, parallel group, longitudinal, pair-matched cluster-randomised controlled superiority trial design. Clusters are defined as villages with 10–75 eligible households, within which households act as the observational unit (see ‘Eligibility criteria {10}’ section for further details).

The DIG programme has identified more than 11,000 eligible households, but only has funding to reach 2700 households under the programme. Randomisation is therefore an equitable way to select households for inclusion. It is also not yet clear that the intervention is effective for people with disabilities and their families. Cluster randomisation was chosen in part because of the nature of the DIG programme, which includes components delivered at the village level.

After random allocation of villages into intervention and control arms, but prior to implementation of the intervention, a baseline survey at household level is conducted (November 2020). The DIG programme is then implemented for 18 months from December 2020 to June 2022. Two endline household surveys are undertaken—the first in July 2022 for participants with a disability to determine the effects of DIG at programme end (endline 1); and a second one in October 2023 for all participants (endline 2), inclusive of participants with disabilities, to assess the longer-term differential effects of the DIG programme between households with and without disabilities.

This work is complemented by a process evaluation to further understand implementation of the DIG programme. The process evaluation is guided by theoretical considerations, such as What underlying theory are we testing with this intervention? What is the theory underlying the design of the graduation programme? And what is the theory underlying the adaptations to make them inclusive? These considerations ground the process evaluation in the relevant wider literature, and support generalisability to future intervention designs that draw on similar theories. To facilitate consideration of theory, an unambiguous articulation of project theory as supposed by the delivery team is developed iteratively in the form of a directed acyclic graph (DAG), based on the theory of change and using set rules for specifying how change is expected to happen.

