### Eligibility criteria {10}

For the purposes of intervention delivery and evaluation, clusters are villages with 10–75 eligible households. This cluster size is necessary for the Village Savings and Loans Associations (VSLAs) and Village Poverty Reduction Committees (VPRCs) (described further under *Intervention description*). To create a cluster, either nearby small villages are grouped or larger villages split to create a manageable cluster, that is, having between 10 and 75 eligible households. For small villages, the geographic distance from its centroid was calculated to the centroid of its adjacent villages, using eligible household’s GPS coordinates. The village concerned was then grouped with adjacent villages having the shortest distance. To split larger villages, we relied on *k*-means clustering to iteratively group neighbouring households, using their GPS coordinates, within a village into clusters. From the 156 villages identified near the BRAC Uganda branch offices in the target districts as potential sites for the DIG programme, 185 of these artificial clusters were created, each with at least 10 eligible households.

Identification of eligible households is based on household-level data collected by the implementing partners (BRAC, HI, and NUWODU). Households are eligible if they meet at least three out of five criterions, as this was felt to be an adequate threshold and would also reflect variations in household experiences of poverty. That is, (1) having a person with disability, (2) being a female-headed household or dependent on earnings from a female member of the household, (3) having children who are out of school, (4) poor housing conditions (floor, roof, and wall), and (5) low productive asset endowment. The Washington Group short set of questions is used to identify households with people with disabilities, based on those that report ‘a lot’ of difficulty on at least one dimension of the six-question set (i.e. walking, seeing, hearing, communicating, understanding and self-care) [8]. Ultra-poor households without a person with disabilities are still eligible for inclusion in the DIG programme in order to ensure there are enough households within each cluster for village-level interventions to operate.

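### The secondary objective is a differential effect by disability, but the only stated method is stratification, which gives no interval or test for the difference between strata

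*Protocol article*

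**What the plan says.** Objectives {7}: "The secondary objective of the impact evaluation is to estimate the differential effect of the DIG programme on per-capita expenditure, livelihood, and social participation", comparing people with disabilities and their families with people without. Trial design {8} gives endline 2 the same purpose: "to assess the longer-term differential effects of the DIG programme between households with and without disabilities".

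The method is in the section on additional analyses {20b}: "These analyses will include stratification by sex, disability status (whether the household has people with disabilities", and further by whether the recipient is the person with disabilities. The stated aim is "to elucidate whether the intervention’s effectiveness varies across these distinct demographic segments". Moderation is mentioned there only for contextual factors in the process evaluation.

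The model in Statistical methods {20a} is a multi-level linear regression "with the difference of the primary or secondary outcomes between follow-up and baseline as the outcome, and intervention status as the exposure". The only adjustment that section foresees is for chance differences between the arms: "controlling for potential imbalance in covariates at baseline". Coefficients are to be reported with 95% CIs.

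Eligibility criteria {10}: "Households are eligible if they meet at least three out of five criterions". Having a person with disability is the first of the five. The others are female headship or dependence on a female earner, children out of school, poor housing, and low productive assets.

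**The concern.** The quantity to be estimated is a difference between two effects, whereas the method named produces the two effects separately. If the results are read stratum by stratum, a significant effect in one and a non-significant effect in the other is easily taken as evidence that the programme works differently, although this pattern is common when the true effects are equal. Conversely, two significant effects are easily taken as equal benefit when the data may not exclude a difference as large as the effect itself. The sample size section is based on the effect among people with disabilities only, so nothing in the article tells the reader how precisely the difference will be known.

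There is also a point of interpretation. Disability counts towards eligibility, so a household with disability enters with two of the other four criteria and a household without needs three. The strata may therefore differ in deprivation, and an observed difference in effect need not be due to disability alone.

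**Working it through.** **Inputs.** From Sample size {14}: 2700 households planned per arm; about 25% of project participants with disabilities; pre-post correlation r = 0.4, 0.6 or 0.8; ICC 0.05 to 0.3; effect 0.1 SD; 185 clusters, taken here as K = 92.5 per arm. Two-sided 5% level. The protocol's own count reproduces: 0.25 × 2700 = 675 per arm, leaving 2025. Subgroup analysis {20b} defines the stratum at household level, so using 675/2025 for it is an assumption.

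**Formulas** (normal approximation, SD units, baseline-adjusted as in the protocol's simulation, common village effect for both strata). With n the stratum size per arm and m = n/K:
- stratum variance: V = 2(1 − r²)/n × [1 + (m − 1) × ICC]
- covariance of the two stratum estimates: C = 2(1 − r²) × ICC/K
- variance of the difference: V1 + V0 − 2C = 2(1 − r²)(1 − ICC)(1/n1 + 1/n0)

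**Worked case, r = 0.6, ICC = 0.05.**
- Disability stratum: m = 7.30, design effect 1.315, SE = √(2 × 0.64/675 × 1.315) = 0.0499; power for 0.1 SD = 52%.
- Other stratum: m = 21.89, design effect 2.045, SE = √(2 × 0.64/2025 × 2.045) = 0.0359; power = 79%.
- C = 2 × 0.64 × 0.05/92.5 = 0.00069, so the estimates correlate at 0.00069/(0.0499 × 0.0359) ≈ 0.39.
- Both strata are significant with probability 0.455 (bivariate normal). Exactly one is significant with probability 0.517 + 0.794 − 2 × 0.455 ≈ 0.40.
- SE of the difference = √(2 × 0.64 × 0.95 × (1/675 + 1/2025)) = 0.0490. Treating the strata as independent gives √(0.0499² + 0.0359²) = 0.0615, about 25% too large. At ICC 0.3 the same comparison is 0.042 against 0.100.

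**Over the protocol's grid**, with a true effect of 0.1 SD in both strata (columns 3–4), and for the interaction (columns 5–6):

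| r | ICC | Power, disability / other | Exactly one significant | SE of difference | Detectable difference at 80% power (2.80 × SE) |
|---|---|---|---|---|---|
| 0.4 | 0.05 | 42% / 68% | 42% | 0.056 | 0.157 |
| 0.4 | 0.3 | 22% / 25% | 15% | 0.048 | 0.135 |
| 0.6 | 0.05 | 52% / 79% | 40% | 0.049 | 0.137 |
| 0.6 | 0.3 | 27% / 31% | 17% | 0.042 | 0.118 |
| 0.8 | 0.05 | 76% / 96% | 23% | 0.037 | 0.103 |
| 0.8 | 0.3 | 44% / 50% | 20% | 0.032 | 0.088 |

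Power for a true interaction of 0.1 SD runs from 43% (r 0.4, ICC 0.05) to 89% (r 0.8, ICC 0.3). If the household disability share were 40–50% (assumed), exactly one stratum would be significant in about 12–36% of trials. A differential effect that varies between villages would lower the interaction power.

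**Eligibility.** A household without disability meets three or four of the other four criteria, and so always has poor housing or low assets. One with disability may meet only two and have neither. If each criterion were independently present with probability 0.5 (assumed), the mean number met would be (6×2 + 4×3 + 1×4)/11 = 2.55 with disability and (4×3 + 1×4)/5 = 3.20 without. At 0.3 the means are 2.26 and 3.10; at 0.7, 2.97 and 3.37. The order is not fixed: prevalence 0.8 in disability households gives 3.26, above the 3.20 for other households at 0.5.

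**The case against.** The article condenses a fuller protocol, and a separate analysis plan may exist. The subgroup section says the analyses will include stratification, which does not exclude an interaction term, and its stated aim is to see whether effectiveness varies. Nowhere does the article say strata will be compared by their p-values. Subtracting the two coefficients already gives a point estimate of the differential effect. All of this stands. It limits the point to the standard error, interval and test of the difference. It does not remove it, because the article does name a method for a formal objective and that method does not deliver the quantity the objective asks for.

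Four stronger readings are tempting, and the documents do not support them.
- That the eligibility rule makes the strata differ in poverty by construction. Only the entry threshold differs by rule; the size and direction of any realised gap depend on prevalences not given.
- That the stratified effects are biased. Randomisation protects each within-stratum effect, and the objective can be read as a descriptive contrast in the eligible population.
- That one stratum is three times the other. That ratio belongs to project participants. Households where someone else, such as a caregiver, is the participant also belong in the disability stratum.
- That the strata disagree in about half of trials. Multiplying the two powers as if independent gives 49% at r 0.6 and ICC 0.05; allowing for shared villages gives 40%.

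**Conclusion.** The concern holds as a mismatch between objective and stated method. A formal secondary objective and the purpose of endline 2 rest on stratification alone, with no estimate of uncertainty for the difference. With equal true effects of 0.1 SD, stratum-wise significance would disagree in about 15–42% of trials, and the detectable interaction of about 0.09–0.16 SD is close to or above the whole effect the trial was sized on. These figures rest on the assumed 675/2025 split, a normal approximation, a common village effect and the protocol's own range of r and ICC. The primary analysis is unaffected. The eligibility rule is a caveat on interpreting the difference and a reason for a supporting analysis; it is not an error in the plan.

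**What to change.** For the secondary objective, fit one model on all endline 2 households with arm, household disability status and arm × disability, plus a random effect for the randomised cluster. Report the interaction with its 95% CI as the estimate of the differential effect, with the stratum effects beside it for description. Treat sex and recipient type the same way.

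Add, as a pre-specified supporting analysis, the interaction adjusted for the other four eligibility criteria and their interactions with arm. State that the unadjusted difference will not be attributed to disability alone.

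The cost is analysis wording only. The criteria were collected at screening, so no new data are needed. The adjusted interaction will have a somewhat wider interval.
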